**Laboratory Samples**

Hospital laboratory can be used to access the following test. If the hospital laboratory has limitation an outside laboratory with NABL accreditations shall be arranged for sample analysis.

- Complete Blood Count with differential (Hemoglobin, Hematocrit, and WBC with differential count) & ESR – **Day-01, 06, EOT (Day15) & 30 of study period**
- Serum Chemistry- Creatinine, Urea, CRP, ALT, AST, Alkaline Phosphatase, Albumin, total bilirubin- **Day-01, Day 06 Only CRP, End of treatment- Day 10 OR Day 15, & End of study period Day 30**.
- Pregnancy test; Serum or Urine human Chorionic Gonadotropin (hCG) - Pregnancy test only required for woman of childbearing potential on the day of randomization (**Day-01**).
- Immunomodulatory markers, IL6, IL7, Interferon α, IgG, IgM- **Day 01, Day 06, End of treatment- Day 10 OR Day 15, & End of study period Day 30**.

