**Secondary Efficacy Endpoint:**

- Proportion of Participants experiencing Treatment-Emergent Adverse Events [Time Frame: First dose date up to 15 days]
- Changes in Haematological and Biochemical parameter like CBC,ESR, CRP, Troponin, Liver function test, Renal function test, [Time Frame: First dose date up to 15 days]
- Changes in inflammatory markers - IL2, IL6, Interferon α, IgG, IgM
- Significant changes in the Chest X-Ray before and after treatment.

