**INVESTIGATIONAL PLAN**

**Overall Study Design**

This is a Randomized controlled, single blinded multi-center, comparative study of ZingiVir-H as an adjuvant therapy in hospitalized adults diagnosed with coronavirus disease 2019 (COVID-19). At inclusion, subjects who meet all inclusion criteria and no exclusion criteria will be assigned, in either therapeutic arm (ZingiVir-H), to receive ZingiVir-H in a dose of 500 mg tablet each consumed once in 3 hours ±1 hour between 6 AM and 9 PM in a given day (6AM, 9AM, 12Noon, 3PM, 6PM, 9PM) for a minimum duration of 10 days to Maximum 15 days OR will be on a Placebo arm to receive placebo (without active ingredients) each consumed once in 3 hours ±1 hour between 6 AM and 9 PM in a given day (6AM, 9AM, 12Noon, 3PM, 6PM, 9PM) for a minimum duration of 10 days to Maximum 15 days. The allocation of study arm is strictly as per the discretion of the Investigator. Whereas both the study groups shall be given standard of care of treatment as per the research site policies or COVID-19 therapeutic management policies. These doses will be administered orally. Blood samples for assessing CBC; safety laboratory tests and immunomodulatory markers will be obtained between baseline assessments (Day-01), during the day-06 of inclusion, at the end of the treatment day-15 and at the end of the study day-30. Safety-related assessments will include reports of adverse events and clinical laboratory test results.

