**Therapeutic dose**:

ONE tablet (500 mg each consumed once in 3 hours ±1 hour between 6 AM and 9 PM in a given day (6AM, 9AM, 12Noon, 3PM, 6PM, 9PM) for a minimum duration of 10 days to Maximum 15 days continuously as per the clinical conditions and disease outcome. Compliance on study drug consumption is important to evaluate the study endpoints.

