**Dosing Visits - Day-1 to EOT (Day15)**

The first dose of study drug must be swallowed within 4 hours from the time study inclusion. The study drug shall be continuing daily each consumed once in 3 hours ±1 hour between 6 AM and 9 PM in a given day (6AM, 9AM, 12Noon, 3PM, 6PM, 9PM) for a minimum duration of 10 days to Maximum 15 days whereas the daily dose shall be administered orally once in 4 ±2 hours interval ie 6 tablets per day.

Following the administration of the first dose record the following:

- Changes in concomitant medications
- Adverse Events/Serious Adverse Events
- Major respiratory failure Events
- Interventions or Surgeries
- Vital signs

**Routine assessment visit and Study drug compliance** – Day 2 to EOT (Day 15)

Following assessments must be made on daily basis for each study subject:

- Vital signs: Pulse – Body temperature, beats per minute (BPM), Blood Pressure (BP) mmHg, Respirations – breaths per minute
- Concomitant medications (including medications, fluids and blood products administered within the 7 days prior to randomization).
- Documentation of any adverse events
- Blood will be obtained for following laboratory tests – only on **Day 06**
  - Complete Blood Count with differential (Hemoglobin, Hematocrit, and WBC with differential count)
  - Serum Chemistry ESR, CRP
  - Immunomodulatory markers, IL6, IL7, Interferon α, IgG, IgM

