**End of treatment visit (EOT) - Day 15**

Following assessments must be made at this EOT visit for each study subject:

- Demographics
- Vital signs: Pulse – Body temperature, beats per minute (BPM), Blood Pressure (BP) mmHg, Respirations – breaths per
- Concomitant medications and Prescribed medications
- Physical Examination including the following: general appearance, Head, Eye, Ear Nose Throat (HEENT), neck, respiratory, cardiovascular, chest, abdomen, lymphatic, musculoskeletal and extremities, skin and neurologic examination.
- Blood will be obtained for following laboratory tests:
  - Complete Blood Count with differential (Hemoglobin, Hematocrit, and WBC with differential count) & ESR
  - Serum Chemistry- Creatinine, Urea, CRP, ALT, AST, Alkaline Phosphatase, Albumin, total bilirubin
  - Immunomodulatory markers, IL6, IL7, Interferon α, IgG, IgM

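### The protocol contradicts itself on the end-of-treatment draw for chemistry and immune markers (Day 10 or 15 versus Day 15), and one reading ties the sampling day to disease outcome

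*Protocol*

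**What the plan says.** Four places in the protocol time the end-of-treatment blood draw.

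- **Laboratory Samples, serum chemistry and immune-marker lines:** "End of treatment- Day 10 OR Day 15, & End of study period Day 30".
- **Laboratory Samples, CBC/ESR line:** "Day-01, 06, EOT (Day15) & 30 of study period".
- **Overall Study Design**, covering CBC, safety laboratory tests and immune markers together: "at the end of the treatment day-15 and at the end of the study day-30".
- **Visit schedule:** "End of treatment visit (EOT) - Day 15", with the full chemistry and immune panel listed for each subject.

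The Therapeutic dose section sets the length of treatment: "for a minimum duration of 10 days to Maximum 15 days continuously as per the clinical conditions and disease outcome".

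The synopsis lists among the secondary endpoints "Changes in Haematological and Biochemical parameter like CBC,ESR, CRP, Troponin, Liver function test, Renal function test", with a window from first dose to 15 days, and changes in inflammatory markers with no day named. Its Statistical Methods section compares continuous variables between groups by t-test and does not mention sampling day.

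**The concern.** Read with the Therapeutic dose section, the Laboratory Samples wording makes the sampling day follow the patient's course after randomization: those who stop on Day 10 are sampled then, the others on Day 15. A subject who stops on Days 11 to 14, which the dosing rule allows, has no draw day at all on this reading. The trial looks for faster improvement, so unequal shares of early stoppers are what an effective product could produce. Shares could also differ without efficacy if whoever decides on stopping knows the arm. That cannot be excluded, because the protocol describes the trial as single blind in one place and as masked to four parties in another.

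The marker comparison would then mix time since randomization with treatment, and randomization does not protect against this because the sampling day is itself a consequence of what follows randomization. For liver and renal chemistry the end-of-treatment draw is the only on-treatment sample after Day 01, since the Day 06 chemistry is limited to CRP. Those safety values would reflect 10 days of exposure in some patients and 15 in others.

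**Working it through.** **1. The plan's own figures.** The protocol gives no calculation on this point. Its only reproducible figure is the sample size: 100 evaluable / (1 − 0.10) = 111.1, rounded up to 112, as stated. That gives about 50 evaluable per arm at 1:1. The stated 50% power cannot be reproduced because no effect size, SD or rate is given. Nothing below depends on it.

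**2. Which draws are affected.**

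| Draw | Laboratory Samples | Overall Study Design | Visit schedule |
|---|---|---|---|
| CBC/ESR, end of treatment | Day 15 | Day 15 (CBC) | Day 15 |
| Chemistry, end of treatment | Day 10 or 15 | Day 15 (safety laboratory tests) | Day 15 |
| Immune markers, end of treatment | Day 10 or 15 | Day 15 | Day 15 |
| CRP and immune markers, early | Day 06 | Day 06 (immune markers) | Day 06 |
| All, end of study | Day 30 | Day 30 | Day 30 |

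Only the second and third rows conflict.

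**3. Size if the Day 10 or Day 15 wording is followed.** None of these inputs is in the documents:

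- The marker is g SD higher on Day 10 than on Day 15, with g = 0.25, 0.5 or 1.0.
- The drug has no effect on the marker on any given day.
- Shares sampled on Day 10 are p1 (ZingiVir-H) and p2 (placebo).
- There are 50 per arm, SD 1 on a given day, and a two-sided t-test at 0.05.

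Expected bias = (p1 − p2) × g.

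Standard error = √{[2 + g²p1(1 − p1) + g²p2(1 − p2)] / 50}.

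Example with p1 = 0.6, p2 = 0.4, g = 1.0: bias = 0.20 SD; SE = √(2.48/50) = 0.223; ratio = 0.90. The normal approximation gives a type I error of 14.6%. Simulation of 20,000 trials gives 14.2%.

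| Shares on Day 10 | Bias in SD (g = 0.25, 0.5, 1.0) | Simulated type I error |
|---|---|---|
| 40% and 40% | 0, 0, 0 | 5.4%, 5.0%, 5.0% |
| 40% and 60% | 0.05, 0.10, 0.20 | 5.6%, 7.7%, 14.2% |
| 30% and 70% | 0.10, 0.20, 0.40 | 7.8%, 16.1%, 44.0% |

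With everyone sampled on one fixed day, simulated type I error is 4.7% to 5.1%.

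**4. The same mechanism can hide an effect.** Suppose the product truly lowers the marker by 0.5 SD, and 60% of its arm but 40% of the placebo arm are sampled on Day 10. The expected difference shrinks to 0.45, 0.40 or 0.30 SD. Simulated power falls from 70.5% with a fixed day to 60.0%, 48.3% or 26.6%.

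**5. Is the direction known?** Step 3 gives every patient the same marker course. If early stoppers recover faster, their CRP probably falls faster too. Assume equal CRP on Day 01, half-lives of 3 days (early stoppers) and 5 days (the others), and shares of early stoppers of 60% and 40%. Relative to Day 01:

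- Early stoppers on Day 10: 2^(−9/3) = 0.125; on Day 15: 2^(−14/3) = 0.039.
- The others on Day 15: 2^(−14/5) = 0.144.
- Arm ratio with mixed days: (0.6 × 0.125 + 0.4 × 0.144) / (0.4 × 0.125 + 0.6 × 0.144) = 0.97.
- Arm ratio with everyone on Day 15: (0.6 × 0.039 + 0.4 × 0.144) / (0.4 × 0.039 + 0.6 × 0.144) = 0.80.

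Half-lives of 3 and 4 days give 1.07 with mixed days against 0.86 on Day 15; 5 and 7 days give 1.03 against 0.90. In these cases mixed sampling shrinks a real difference or slightly reverses it. The distortion persists, but its sign depends on unknown marker courses.

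**The case against.** The strongest reply is that Overall Study Design and the visit schedule both fix the draw on Day 15, with the same panel due in each subject. If they govern, no sampling-day bias arises. That stands, and it is why the defect is a contradiction to reconcile and not a settled schedule. It does not dispose of the point, because a site working from the Laboratory Samples section would still draw on Day 10.

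A reader might infer that the faster-recovering arm must show a falsely raised CRP and lowered IgG. The documents do not support this. They give no Day 10 shares and no marker courses, and that direction follows only if fast and slow recoverers share one curve (step 5). With equal shares there is no bias.

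It can also be said that the secondary endpoint names no end-of-treatment contrast, and that the visit and model used, including any adjustment for sampling day, may be left to an analysis plan. That is fair as to the model. But no analysis plan can recover Day 15 samples that were never drawn; the collection day is a protocol decision.

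Finally, the scope is limited. The primary ordinal endpoint is fixed on Day 15, and the Day 06 and Day 30 comparisons use fixed days.

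**Conclusion.** The point holds as an internal contradiction with a conditional consequence. The Laboratory Samples section conflicts with its own CBC/ESR line, with Overall Study Design and with the visit schedule on when chemistry and immune markers are drawn at end of treatment. Following its wording makes the sampling day depend on a post-randomization outcome.

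Bias then needs two things: unequal shares sampled on Day 10, and a marker that moves between Days 10 and 15. In the 40% and 60% illustration, type I error lies between a negligible excess (5.6%) and a material one (about 14%). These figures show the possible scale under assumed inputs and are not estimates for this trial. The secondary laboratory comparisons and the end-of-treatment safety chemistry are exposed; the efficacy conclusion on the primary endpoint is not. The contradiction should be corrected because the remedy is cheap and samples not drawn cannot be recovered.

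**What to change.** Reconcile the Laboratory Samples section with Overall Study Design and the visit schedule: draw serum chemistry and immune markers on Day 15 in all subjects, whatever the day of last dose. State that the end-of-treatment change in the secondary laboratory and marker endpoints is Day 15 minus Day 01. Label any sample taken when study drug stops as additional and keep it for safety review. This alters the sampling day only and leaves treatment duration as it is.

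The change is to two lines of the Laboratory Samples section plus a clarifying clause in the endpoint. CBC/ESR is already due on Day 15 in every subject, so for most the added assays use an existing draw. The downside is Day 15 assays for patients who stopped study drug earlier, and possibly a return draw for those already discharged.

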**Visit Schedule and Assessments**

**Screening / Randomization Visit – Day 01**

Subjects must meet the inclusion criteria and have none of the exclusion criteria in order to be eligible for randomization in this study. Subjects who meet all eligibility criteria, and have signed informed consent will be discussed randomize and move on to the Baseline study visit. Once the subject is randomized the sponsor representative or the study Investigator will provide the study staff with a unique randomization number for the subject.

Following assessments must be made at this Baseline visit for each study subject:

- RT-PCR test assuring the subjects test positive for COVID-19.
- Demographics
- Medical history (all known information regarding the subject’s health history/relevant surgeries/interventions prior to signing the informed consent).
- Vital signs: Body temperature, Pulse – beats per minute (BPM), Blood Pressure (BP) mmHg, Respirations – breaths per
- Concomitant medications (including medications, fluids and blood products administered within the 7 days prior to randomization).
- Documentation of any other infection if available (site of infection and, if available: positive culture results, prior antibiotics, sensitivity of cultured organism to antibiotics, nonmedical treatment such as surgery or drainage).
- Physical Examination including the following: general appearance, Head, Eye, Ear Nose Throat (HEENT), neck, respiratory, cardiovascular, chest, abdomen, lymphatic, musculoskeletal and extremities, skin and neurologic examination. Height and weight (baseline dry weight).
- Blood will be obtained for following laboratory tests:
  - Complete Blood Count with differential (Hemoglobin, Hematocrit, and WBC with differential count) & ESR
  - Serum Chemistry- Creatinine, Urea, CRP, ALT, AST, Alkaline Phosphatase, Albumin, total bilirubin
  - Pregnancy test; Serum or Urine human Chorionic Gonadotropin (hCG) - Pregnancy test only required for woman of childbearing potential on the day of randomization
  - Immunomodulatory markers, IL6, IL7, Interferon α, IgG, IgM

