**Masking:**

Quadruple (Participant, Care Provider, Investigator, Outcomes Assessor)

**Duration of Treatment**: Minimum of Ten days to Maximum of Fifteen (15) days of study drug regimen and a follow-up on 30^th^ day from the day of baseline.

**Reference Therapy, Dosage and Mode of Administration**: Placebo and Standard of Care (SOC)

Placebo for this study is supplied as identically labeled, tablets. Placebo will also be required to be maintained in controlled environment as IP. Placebo must be consumed according to the same procedures and guidelines as ZingiVir-H.

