**Blinding**

Study drug will be assigned and administered in a Single blind fashion.

In the event of a medical emergency where it is imperative to know which treatment arm the subject was randomized to in order to make future treatment decisions, the Investigator may break the blind for an individual subject after getting approval from study monitor or sponsor. If any adverse events causing the need for subject unblinding, will be handled as a serious adverse event in accordance with the procedures outlined in this protocol. Any broken blind will need to be clearly justified, explained by a comment within the Case Report Form (CRF), and captured on the Serious Adverse Event Form.

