**Data Management**

**Documentation**

Case report forms (CRFs) will identify each subject by subject number (compilation of site number and randomization number) and subject's initials (per local regulatory guidelines). Originals or copies of all source documents, and correspondence will be kept on file at the investigational site.

The data required by the protocol will be recorded in the appropriate pages of CRFs. All source data will be available to the study monitor who may perform a 100% data check (comparison of the data recorded in the eCRF with those in the source documents). The source data will also be available for an audit by the Sponsor and all applicable regulatory agencies at any time.

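### Allocation concealment is not assured: the Investigator, who recruits, may also issue the randomization number, and nothing in the protocol keeps the sequence from that person

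*Protocol*

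**What the plan says.** The section Screening / Randomization Visit – Day 01 sets the order of events: "Subjects who meet all eligibility criteria, and have signed informed consent will be discussed randomize and move on to the Baseline study visit". It then names two possible issuers: "the sponsor representative or the study Investigator will provide the study staff with a unique randomization number for the subject". Under Documentation, that number becomes part of the patient's identifier, the "subject number (compilation of site number and randomization number").

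Three other statements bear on who may know the arm:

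- Overall Study Design: "The allocation of study arm is strictly as per the discretion of the Investigator".
- Blinding: "Study drug will be assigned and administered in a Single blind fashion". The title and Overall Study Design also say single blind.
- Masking, in both the synopsis and the body: "Quadruple (Participant, Care Provider, Investigator, Outcomes Assessor"), together with "Placebo for this study is supplied as identically labeled, tablets".

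The Blinding section also requires the Investigator to obtain approval from the study monitor or sponsor before breaking the blind for a patient.

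The synopsis gives a 1:1 ratio and up to 5 sites recruiting competitively. The protocol names no list holder, central system, sealed envelopes or coded packs.

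**The concern.** Generating a random sequence and concealing it are separate safeguards. Concealment means that whoever decides whether a candidate enters the trial cannot know the next assignment. The protocol gives an issuing role to the Investigator, who also judges eligibility and recruits, and does not separate that role from the list.

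If the next arm can be foreseen, a candidate can be delayed, skipped or hurried according to prognosis. The arms then differ at baseline before any treatment is given. The Day 15 odds ratio on the 7-point scale absorbs that difference, and the t-test, rank-sum test and Fisher's exact test named under Statistical Methods make no adjustment for it. Concealment cannot be restored once patients are enrolled.

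This differs from the sentence on Investigator discretion in Overall Study Design. Read literally, that sentence leaves no random list to conceal. If it were deleted and a proper 1:1 list produced, the Day 01 section would still let the recruiting Investigator issue from that list.

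**Working it through.** **1. The plan's own figure.** 100 evaluable / (1 − 0.10) = 111.1, rounded up to 112, as stated. The point does not depend on it. The protocol gives no figure for predictability of allocation, so the rest compares sections and then illustrates.

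**2. What the sections establish together.**

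| Question | Protocol text | Settled? |
|---|---|---|
| Who issues the number? | Sponsor representative or Investigator (Day 01 visit) | Yes; a recruiter is allowed |
| When? | After eligibility, consent and randomization (Day 01 visit) | Yes |
| Who generates and holds the list? | Not stated | No |
| Does the number reveal the arm? | Not stated | No |
| Is the Investigator masked? | No under single blind in its usual sense (patient only); yes under Masking | Contradictory |

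The first row is a stated procedure. The last three show that nothing else in the document dependably protects the sequence.

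**3. How predictable the next arm could be.** The protocol states no block size, so these sizes are assumptions. In 1:1 permuted blocks of size 2b, someone who knows all past assignments knows a share 1/(b + 1) of the next ones with certainty. Best-guess accuracy comes from simulation.

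| Block size | Certain, 1/(b + 1) | Best guess correct |
|---|---|---|
| 2 | 1/2 = 50% | about 75% |
| 4 | 1/3 = 33% | about 71% |
| 6 | 1/4 = 25% | about 68% |
| 8 | 1/5 = 20% | about 67% |

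The two extremes are 100% if the Investigator holds an open list, and 50% (a coin toss) if numbers map to indistinguishable coded packs and the Investigator is truly masked. The protocol does not say where in this range the trial lies.

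**4. What steering could do.** The only inputs from the protocol are 50 evaluable per arm (100/2) and the rank-sum test at the two-sided 5% level. Assumptions: no drug effect; full foresight; half of candidates have a poorer prognosis; a Day 15 distribution from death to discharge of 3/3/4/8/15/17/50%; and a proportional-odds ratio between prognosis groups of 3 to 5.

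Let q be the chance of passing over a poorer candidate before an active slot and, in two-way steering, a better candidate before a placebo slot. The better-prognosis share in the active arm is then 0.5 / (0.5 + 0.5(1 − q)) = 1/(2 − q). In two-way steering the placebo share is 1 − 1/(2 − q); in one-way steering it stays at 50%.

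- q = 0.3: 1/1.7 = 59%, against 41% (two-way)
- q = 0.5: 1/1.5 = 67%, against 33% (two-way)

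| Steering | Chance of a false result favouring ZingiVir-H |
|---|---|
| None | about 2.4% |
| Two-way, q = 0.1 | about 3–4% |
| Two-way, q = 0.3 | about 7–11% |
| Two-way, q = 0.5 | about 15–27% |
| One-way, q = 0.3 | about 4–6% |
| One-way, q = 0.5 | about 7–10% |

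The ranges span odds ratios of 3 to 5 and agree across repeated simulations of 4,000 to 8,000 trials per setting.

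**The case against.** A reader might infer that the list is open to the Investigator and that the next arm can be foreseen. The document does not support that. No section says that the Investigator generates, holds or sees a list, or that the number reveals the arm. Handing a number to study staff is equally consistent with relaying one obtained elsewhere. Both Masking sections name the Investigator as masked, the placebo is identically labelled, and a rule requiring approval to break the blind makes little sense if the Investigator already knows the arm. The composition of the subject number does not show who knows the arm either. All of this stands, and it is why the conclusion is conditional.

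The order of events is also a fair objection: "Once the subject is randomized the sponsor representative or the study Investigator will provide" the number, so eligibility and consent come first. It would be wrong to say that no lock-in step exists. But this order does not conceal the sequence, because someone holding the list would know its next entry before approaching a candidate.

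List generation and pack coding are often kept in a separate randomization plan, so their absence alone would be no finding. What remains is the stated permission for the Investigator to issue the number, in a protocol that contradicts itself on whether the Investigator is masked.

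Finally, the simulated rates depend on assumed behaviour. They describe deliberate steering with full foresight and do not follow from the protocol text. With mild steering (q = 0.1) the effect is small.

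**Conclusion.** The point holds in conditional form. The protocol permits a recruiter to issue the randomization number and contains no dependable safeguard that keeps the sequence from that person, so concealment is not assured. If the Investigator holds the list or knows past assignments, the next arm could be foreseen, wholly with an open list and in part with small blocks. If numbers map to indistinguishable coded packs and the Investigator is masked, there is no foresight and no bias from this source.

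The protocol does not fix the size of any bias. The illustrative rise to about 7–11% at 30% two-way steering rests on the assumed prognosis mix, outcome distribution, odds ratio, steering rate and full foresight. The change is worth making because it is cheap, and the named tests would not correct the bias if it arose.

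**What to change.** In Screening / Randomization Visit – Day 01:

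- Remove the Investigator as issuer, along with any sponsor representative involved in enrolment.
- State that a party independent of enrolment, treatment and outcome scoring generates and holds a computer-generated 1:1 list.
- State that each patient is assigned the next sequentially numbered, identical-looking coded pack, and only after eligibility and consent have been recorded.

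Then reconcile this section with Overall Study Design, Blinding and both Masking sections, so that the protocol gives one answer on who allocates and one on who is masked.

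The cost is a short amendment and numbered packs prepared off site, with pack preparation and stock control at up to 5 sites as the small downside. It needs no extra patients, visits or site staff.
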